## Abstract

**Background:**

In up to 30% of patients with ischemic stroke no definite etiology can be established**.** A significant proportion of cryptogenic stroke cases may be due to non-stenosing atherosclerotic plaques or low grade carotid artery stenosis not fulfilling common criteria for atherothrombotic stroke. The aim of the CAPIAS study is to determine the frequency, characteristics, clinical and radiological long-term consequences of ipsilateral complicated American Heart Association lesion type VI (AHA-LT VI) carotid artery plaques in patients with cryptogenic stroke.

**Methods/Design:**

300 patients (age >49 years) with unilateral DWI-positive lesions in the anterior circulation and non- or moderately stenosing (<70% NASCET) internal carotid artery plaques will be enrolled in the prospective multicenter study CAPIAS. Carotid plaque characteristics will be determined by high-resolution black-blood carotid MRI at baseline and 12 month follow up. Primary outcome is the prevalence of complicated AHA-LT VI plaques in cryptogenic stroke patients ipsilateral to the ischemic stroke compared to the contralateral side and to patients with defined stroke etiology. Secondary outcomes include the association of AHA-LT VI plaques with the recurrence rates of ischemic events up to 36 months, rates of new ischemic lesions on cerebral MRI (including clinically silent lesions) after 12 months and the influence of specific AHA-LT VI plaque features on the progression of atherosclerotic disease burden, on specific infarct patterns, biomarkers and aortic arch plaques.

**Discussion:**

CAPIAS will provide important insights into the role of non-stenosing carotid artery plaques in cryptogenic stroke. The results might have implications for our understanding of stroke mechanism, offer new diagnostic options and provide the basis for the planning of targeted interventional studies.

**Trial Registration:**

NCT01284933

## Background

Ischemic stroke is one of the leading causes of disability and death in industrialized countries [1]. Current etiologic classification systems like TOAST (trial of Org 10172 in Acute Stroke Treatment) [2] or A-S-C-O [3] assign stroke causes to one of four major categories: large artery atherosclerosis (LAA), cardioembolism (CE), small vessel disease (SVD) or stroke of other determined etiology. However, in up to 30% of cases the etiology remains unknown (cryptogenic stroke) even in well characterized patients [4,5]. A review by Amarenco suggested that a significant proportion of these cases may be due to non-stenosing atherosclerotic plaques or low grade cervical artery stenosis not fulfilling common criteria for atherothrombotic stroke [6].

Previous histopathological examinations have demonstrated a role of plaque rupture in myocardial infarction [7] as well as atherosclerotic stroke [8]. Plaque rupture depends on plaque vulnerability rather than plaque size. Plaques with a lipid rich necrotic core, a thin fibrous cap, marked inflammation and intraplaque hemorrhage have been shown to predispose to rupture and thromboembolic complications [9-11]. Despite the obvious association of plaque composition and its vulnerability, current treatment algorithms for carotid artery atherosclerosis use stenosis grade as decision criterion whereas plaque characteristics are usually not considered [12,13].

High-resolution black-blood carotid magnetic resonance imaging (carotid MRI) allows non-invasive characterization of atherosclerotic plaques by the assessment of plaque size, plaque composition, and plaque morphology with good correlation to histopathology [14,15]. Complicated American Heart Association lesion type (AHA-LT) VI plaques are characterized by plaque surface rupture, luminal thrombosis and intra-plaque hemorrhage [14]. Furthermore, progression of atherosclerotic disease burden can be monitored non-invasively [16,17].

Previous MR plaque imaging studies on patients with carotid artery stenosis have revealed an association between the presence of complicated AHA-LT VI features and ischemic events in cross-sectional [18,19] and longitudinal studies [20,21]. However, most of these studies were performed in patients with high grade stenosis [20,21] and mixed cohorts of both asymptomatic and symptomatic patients [18,22]. Furthermore, they used a broader definition of the index event [19], and time between symptoms and carotid plaque MRI was up to 3 months [23]. In a prospective pilot study on 32 cryptogenic stroke patients with non-stenosing carotid artery plaques we recently found a prevalence of 37% for complicated AHA-LT VI plaques ipsilateral to the ischemic stroke compared to the contralateral side, where no AHA-LT VI plaques were found (p = 0.001) [24]. These findings suggest a possible causative role of complicated AHA-LT VI plaques in patients with cryptogenic stroke.

We thus initiated the current prospective CAPIAS study with the primary aim to determine the prevalence of complicated AHA-LT VI plaques ipsilateral to an acute ischemic stroke in patients with a cryptogenic stroke. Secondary outcome measures include the association of complicated AHA-LT VI plaques with specific infarct patterns, biomarkers and aortic arch plaques, the evaluation of recurrence rates of ischemic events up to 36 months and rates of new ischemic lesions on cerebral MRI (including clinically silent lesions) after 12 months as well as the evaluation of the influence of specific AHA-LT VI plaque features on the progression of atherosclerotic disease burden.

### Patient population - Inclusion and exclusion criteria

Patients of both genders older than 49 years presenting with neurological symptoms compatible with an acute unilateral anterior circulation infarct within the last seven days are recruited through certified stroke units at the participating centers. DWI positive lesions in the territory of a single internal carotid artery (ICA) on cerebral MRI and the presence of plaques with ≥ 2 mm thickness on one of the carotid arteries as defined by ultrasound are required for inclusion. Patients with high-grade carotid artery stenosis (≥70% NASCET) are excluded from the study as these patients usually undergo immediate invasive treatment (carotid endarterectomy or carotid artery stenting) following current guidelines. Additional exclusion criteria include bilateral ischemic lesions and infarcts within the posterior circulation. For detailed inclusion and exclusion criteria see Table 1.

**Table 1 T1:** Inclusion and exclusion criteria

**Inclusion criteria**	**Exclusion criteria**
• Age > 49 years old	• Primary referral to an outside hospital
• Acute ischemic stroke or transient ischemic attack (TIA)	• DWI positive lesions outside the territory of a single internal carotid artery
• Neurological symptoms compatible with a stroke or TIA in the territory of the internal carotid artery	• Surgical procedure within 24 hours preceding the MRI
• Onset of symptoms within the last 7 days	• History of radiation to the neck area
• 1 or more acute ischemic lesion(s) visible on MR diffusion-weighted imaging (DWI) in the territory of a single internal carotid artery	• Carotid artery stenosis ≥70% (NASCET) ipsilateral to the stroke or TIA as defined by ultrasound (systolic peak flow velocity ≥ 300 cm/s)
• Presence of carotid artery plaques in the ipsi- or contra-lateral carotid artery as defined by ultrasound (plaque thickness at least 2 mm; located within 1 cm proximal or distal to the carotid bifurcation)	• Creatinine levels > 2 times the upper limit of the standard range of the respective laboratory within the last 30 days prior to MRI and Renal clearance < 30 ml/minute
• Written informed consent	• Standard contra-indications for MRI

In our study “Cryptogenic stroke” is defined as a stroke `of undetermined origin’ according to TOAST classification, which is equivalent to the absence of grade 1 pathology according to A-S-C-O. Thus, patients with concurrent etiologies will be analyzed as a separate group. Patients with cardioembolic stroke or small vessel disease represent the negative control group and patients with large artery atherosclerosis (50-69% stenosis) serve as positive control.

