#### *Carotid MRI*

All subjects are imaged twice (baseline and 12 month follow up) using a multi-sequence protocol [31] (Time-of-flight MR angiography (TOF-MRA), axial pre- and post- contrast black-blood T1-, PD- and T2- weighted sequences with fat suppression; best in-plane resolution 0.5 × 0.5 mm^2^) at 3 Tesla (Siemens Verio, Siemens Healthcare, Erlangen, Germany) with a dedicated 4-channel surface coil (Machnet B.V., Eelde, the Netherlands). Parallel imaging is used for all sequences with a parallel acquisition technique (PAT) acceleration factor of 2 for T1-, PD- and T2- weighted sequences. The protocol results in a total imaging time of 22:43 minutes for the carotid MRI. Gadolinium-DTPA-BMA (Gadobutrol, Bayer Schering, Leverkusen, Germany) of 0.1 mmol/kg (0.1 ml/kg) is given at a rate of 3 ml/s. Post-contrast T1w imaging is performed approximately 5 minutes after intravenous injection of the contrast agent. Fat suppression is used for pre- and post-contrast T1w, PDw, and T2w images to reduce signals from subcutaneous and perivascular fat. Each scan covers 30 mm (2 mm slice thickness × 15 matched images across the 5 sequences).

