This study also has limitations. Secondary prevention during follow up will differ among study participants depending on previous medication and stroke etiology. Patients with LAA or SVD are treated with antiplatelet agents, whereas patients with a cardioembolic etiology usually receive anticoagulants. Also, this study offers no information on the natural history of carotid plaques as all patients receive statin treatment for secondary stroke prevention. As demonstrated in several studies, statins influence the development of plaque burden, intraplaque hemorrhage and inflammation [39]. Another limitation is the additional scan time of the study-related MRI protocol, which may result in movement artifacts and severely affected stroke patients may refuse receiving an additional MRI.

So far, clinical and radiological baseline data of 79 patients have been analyzed. Stroke subtyping using the TOAST criteria showed the following distribution: 14% of subjects had LAA, 27% had CE, 13% had SVD, 5% had multiple potential causes (MPC) and 40% had cryptogenic stroke (Table 3). The small number of patients with LAA, the absence of other stroke causes and the high percentage of cryptogenic stroke result from our inclusion and exclusion criteria. Thus, the number of patients with LAA is smaller than expected as patients with ≥ 70% stenosis are excluded. Furthermore, we only include patients with advanced atherosclerotic disease, defined as plaques ≥ 2 mm in the carotid arteries, which might also explain the smaller than expected%-ages of patients with CE and SVD and the absence of patient with other stroke causes e.g. carotid artery dissection. Consistent with this notion, patients with cryptogenic stroke compromised almost half of our patient population, suggesting a potential link between atherosclerotic disease and the underlying cause of the ischemic stroke.

**Table 3 T3:** Baseline characteristics of the first 79 patients enrolled in Munich

Age in years (median, Q1-Q3)		74 (68–83)
Female (n,%)		25 (32)
Systolic blood pressure at admission (mean, SD)		142 (19)
Diastolic blood pressure at admission (mean, SD)		78 (11)
BMI (mean, SD)		26 (3)
Pre stroke living condition (n,%)		
	At home alone	23 (32)
	At home with family or friends	46 (64)
	Institutionalized	2 (3)
NIHSS at admission (n,%)		
	0–4	51 (65)
	5–15	24 (30)
	≥16	4 (5)
mRS on admission (n,%)		
	0–2	47 (60)
	3-5	31 (40)
B I on admission (n,%)		
	0–19	5 (6)
	20–49	15 (19)
	50–74	6 (8)
	75–99	16 (20)

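### Table 1 joins its two renal limits with 'and', so a clearance below 30 ml/minute does not by itself exclude a patient from the gadolinium carotid MRI

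*Protocol article*

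**What the plan says.** Table 1 (Methods, Patient population) puts both renal limits in one exclusion bullet. The first half reads "Creatinine levels > 2 times the upper limit of the standard range of the respective laboratory within the last 30 days prior to MRI". The clearance limit follows in the same bullet, attached by 'and': "within the last 30 days prior to MRI and Renal clearance < 30 ml/minute". No other exclusion mentions renal function. The only other bullet bearing on scan safety is "Standard contra-indications for MRI", which names neither the kidneys nor contrast.

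The Carotid MRI section sets the exposure. It states "All subjects are imaged twice (baseline and 12 month follow up) using a multi-sequence protocol", and the sequence set includes "axial pre- and post- contrast black-blood T1-, PD- and T2- weighted sequences with fat suppression". The gadolinium dose is given as "of 0.1 mmol/kg (0.1 ml/kg) is given at a rate of 3 ml/s". The Discussion treats this imaging as a burden added by the study: "Another limitation is the additional scan time of the study-related MRI protocol".

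**The concern.** An exclusion built as 'A and B' removes only patients who meet both conditions. Here, a clearance below 30 ml/minute has no effect unless creatinine is also above 2 x ULN.

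Serum creatinine falls with muscle mass, so an older, light patient can have low clearance while creatinine stays under twice the ULN. For such patients the creatinine condition switches off the clearance limit. They would then be eligible for contrast given in a scan that the study itself adds, in a study that is otherwise observational.

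The bullet gives no rationale. That it is meant to protect against contrast exposure is an inference from the Carotid MRI section. The stake is patient safety only.

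**Working it through.** **Step 1: the logic of the bullet.** Let A be creatinine > 2 x ULN and B be clearance < 30 ml/minute.

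| A | B | Literal text ('and') | With 'or' |
|---|---|---|---|
| yes | yes | excluded | excluded |
| yes | no | eligible | excluded |
| no | yes | **eligible** | excluded |
| no | no | eligible | eligible |

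The third row is the problem. The next question is whether anyone can fall in it.

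**Step 2: inputs.**
- From Table 3 (first 79 patients): age median 74, quartiles 68 and 83; BMI mean 26, SD 3; 25 women (32%).
- Assumed, because the document gives none of them: the Cockcroft-Gault formula; heights of 1.60 m (women) and 1.72 m (men); ULN of 0.9-1.1 mg/dl (women) and 1.1-1.3 mg/dl (men).
- Weight at BMI 26: 26 x 1.60² = 66.6 kg for women and 26 x 1.72² = 76.9 kg for men.

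**Step 3: formula.** Clearance = (140 − age) x kg / (72 x creatinine), multiplied by 0.85 for women. Creatinine of exactly 2 x ULN is the highest value that does not meet condition A, so it gives the lowest clearance at which a patient with A unmet stays eligible. A gap exists only where that clearance is below 30.

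Example, woman aged 83 with ULN 0.9: 57 x 66.6 x 0.85 / (72 x 1.8) = 24.9 ml/minute.

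**Step 4: clearance at 2 x ULN, BMI 26.** The range runs from the highest to the lowest assumed ULN.

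| Patient | Clearance (ml/minute) | Gap below 30? |
|---|---|---|
| Woman 83 | 20.4-24.9 | yes |
| Woman 74 | 23.6-28.8 | yes |
| Woman 68 | 25.7-31.4 | depends on ULN |
| Man 83 | 23.4-27.7 | yes |
| Man 74 | 27.1 / 29.4 / 32.0 at ULN 1.3 / 1.2 / 1.1 | depends on ULN |
| Man 68 | 29.6-35.0 | essentially none |

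**Step 5: sensitivity to body size.**
- BMI 23 (mean − 1 SD): woman 83, 18.0-22.0; man 74, 24.0-28.4.
- BMI 29 (mean + 1 SD): woman 83, 22.7-27.8; man 83, 26.1-30.9; man 74, 30.2-35.7 (no gap).
- Setting clearance to 30 and solving for weight, the gap closes above 69-85 kg (woman 74), 80-98 kg (woman 83), 72-85 kg (man 74) and 83-99 kg (man 83), depending on ULN.

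**Step 6: width of the gap.** At BMI 26, clearance drops below 30 at a creatinine of (140 − age) x kg / (72 x 30), times 0.85 for women. The creatinine band that is below the clearance limit yet still eligible is:
- Woman 83: from 1.49 up to 1.80 mg/dl (ULN 0.9) or 2.20 (ULN 1.1).
- Woman 74: from 1.73 up to 1.80 or 2.20.
- Man 83: from 2.03 up to 2.20 (ULN 1.1) or 2.60 (ULN 1.3).
- Man 74: from 2.35 up to 2.40 at ULN 1.2; none at ULN 1.1.

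Repeating Step 4 with slightly larger patients (68 kg and 80 kg) gives the same pattern: a gap across the whole ULN range for women aged 74 and 83 and men aged 83, only at the highest ULN for a man aged 74, and none for a man aged 68.

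**The case against.** The best defence is that 'and' in a column of exclusions often just lists two excluded states. The capital letter on the clearance term in mid-sentence suggests a second item that was run into the bullet. On that view the investigators meant two separate exclusions and nobody chose to admit patients below 30 ml/minute. This is plausible. It does not rescue the text, because a site applying Table 1 as written gets the conjunctive rule, and every other exclusion stands in its own bullet.

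Sites might also catch such patients through the general MRI contraindication bullet or local contrast rules. They might, but that bullet names neither renal function nor contrast, and it cannot be relied on to override an explicit renal rule beside it. Nor is this detail left to a fuller protocol: the article sends the reader to Table 1 for the detailed criteria, and the criterion is stated there.

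Three further limits stand. The figures rest largely on a formula, ULNs and heights from outside the document. Some of the creatinine bands are narrow, and the number of patients in them may be small or nil. The document does not itself describe a harm from contrast at low clearance; it only sets 30 ml/minute as a limit.

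**Conclusion.** The concern holds. As written, the rule does not enforce its own clearance limit for every patient below it. Under the stated assumptions the unprotected group is not empty: at BMI 26 it includes women of 74 and women and men of 83 whatever ULN is used within the assumed range. These ages are the median and upper quartile of the first 79 patients. The gap is small or absent in a man of 74 of average weight, and in most heavier patients.

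The number affected cannot be derived from the document. The existence of the gap follows from the wording alone; its location depends on the assumed formula, ULNs and heights. It should be corrected as a safety matter, with no consequence for the statistical design.

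**What to change.** In Table 1, replace 'and' with 'or', or list renal clearance < 30 ml/minute as a separate exclusion bullet. Either makes low clearance exclude on its own.

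The edit is one word or one bullet. The cost is that a few patients with clearance below 30 ml/minute, mainly older and lighter ones, become ineligible. With 'or', or with creatinine kept as an exclusion in its own right, patients with creatinine above 2 x ULN but clearance of 30 or more are excluded as well. If 'or' was the intent all along, the change only records it.

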### Primary outcome

The primary outcome of the CAPIAS study is the prevalence of complicated AHA-LT VI plaques ipsilateral to an acute ischemic stroke in the territory of a single carotid artery in patients with a cryptogenic stroke. The analyses will include a comparison of the prevalence of complicated AHA-LT VI plaques ipsilateral versus contralateral to the ischemic stroke and a comparison of complicated AHA-LT VI plaques in patients with cryptogenic stroke as compared to patients with defined stroke etiology.

### Secondary outcomes

Secondary outcomes include the association of complicated AHA-LT VI plaques with specific infarct patterns (territorial infarcts, multiple embolic infarcts, small lacunar lesions), with aortic arch plaques as determined by transoesophageal echocardiography or computed tomography angiography (CTA) and their association with biomarkers derived from serum and plasma. Furthermore, we will evaluate the recurrence rate of ischemic events and the rate of new ischemic lesions on brain MRI in patients with complicated AHA-LT VI plaques after twelve months follow up. In addition, we will investigate whether specific features of complicated AHA-LT VI plaques, such as intraplaque hemorrhage and thin or ruptured fibrous cap are associated with an increased progression rate of atherosclerotic disease burden after twelve months.

Recurrent ischemic events include cerebrovascular and cardiovascular events. Cerebrovascular events are defined either clinically (TIA, amaurosis fugax or stroke), by brain MRI alone (new ischemic lesion on brain MRI) or on the combined assessment of clinical findings and brain MRI. Furthermore, the most likely cause of the recurrent cerebrovascular event is classified according to the ASCO and TOAST classifications. Unilateral events in the anterior circulation will be included in the final analysis to estimate the risk of recurrent events in patients with AHA-LT VI plaques. Recurrent ischemic events in other territories, bilateral events and cardiovascular events (myocardial infarction, vascular death) are recorded during follow-up to evaluate if patients with complicated AHA-LT VI plaques have a higher overall atherosclerotic disease burden.

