### Sample size

Based on a pilot study by Freilinger et al. [24], we estimated that 40% of ipsilateral carotid artery plaques in patients with a cryptogenic stroke are complicated AHA-LT VI plaques. Thus, in 100 patients with cryptogenic stroke the prevalence can be assessed with a precision of +/− 10%. Our unpublished pilot data indicate a prevalence of complicated AHA-LT VI plaques in patients with defined stroke etiology of about 10%. To determine this difference with a power of 80% and 5% level of significance, 32 patients of each group (cryptogenic and control group) would be sufficient. Assuming a prevalence of complicated AHA-LT VI plaques of 30% in the cryptogenic stroke group, 64 patients in each group are needed.

The recurrence rate of ischemic stroke associated with complicated AHA-LT VI plaques will be determined as the time period until the next ischemic event. Assuming a recurrence rate of ischemic events of 8% [35] within 12 months following the index stroke and a hazard ratio of AHA-LT VI plaques ≥ 5 [19,34,35], 300 patients will be enough to demonstrate a significant difference in event rates between patients with and without AHA-LT VI plaques.

Previous longitudinal studies, which demonstrated associations of intraplaque hemorrhage with accelerated plaque progression and with new surface disruption, were able to show those associations with much smaller sample sizes [21,36]. Thus 300 patients will provide sufficient power to detect effects of certain plaque features on plaque progression.

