**Figure 1 F1:**
[figure not shown]
**Axial images of specific AHA-LT VI plaque features in a patient with acute ischemic infarct.** High-resolution black blood MRI of the carotid arteries demonstrate a large eccentric plaque with <50% stenosis in the right carotid artery, hyperintense on T1w, T2w and PDw sequences consistent with fresh intraplaque hemorrhage (**A**, arrow). Axial images 0.6 cm above the bifurcation show an area attached to the plaque, which is hypo- to isointense on T1w + CM, PDw and TOF, consistent with a mural thrombus (**B**, arrow). (T1w: T1-weighted black blood sequence, PDw: PD-weighted sequences, T2w: T2-weighted sequence, TOF: Time-of-flight MR angiography, T1w + CM: T1-weighted black blood sequence after contrast administration).

All carotid and brain MRI examinations will be evaluated by two radiologists blinded to the clinical status. In case of discordant results, a consensus decision will be made. Image quality is rated on a five point scale (1 = worst, 5 = best), with MRIs ≥3 included for further analysis [31].

New ischemic lesions on brain MRI during follow up are defined as hyperintense lesions clearly visible on T2 weighted sequences.

All statistical analyses will be performed using SPSS and SAS. For determination of differences in prevalence of complicated AHA-LT VI plaques between patients with cryptogenic stroke and stroke with defined etiology the Chi square test will be used. Differences in the prevalence of complicated AHA-LT VI plaques ipsi- and contralateral to the ischemic stroke will be calculated using the McNemar Test. For the cross-sectional analysis the prevalence of AHA-LT VI plaques in patients with territorial infarcts, multiple embolic infarcts and small lacunar lesions will be compared. Furthermore, the difference in prevalence of AHA-LT VI plaques in patients with aortic arch plaques < 3 mm and > 3 mm will be determined. Data from the serial plaque study are analyzed in accordance to previous studies [38]. The effect of plaque morphology on cerebrovascular (TIA, amaurosis fugax and stroke) and cardiovascular events (myocardial infarction, vascular death) will be assessed using Cox proportional-hazards regression analysis. Cohen’s kappa test will be employed to evaluate the intra- and inter-reader agreement for identification of AHA-LT VI.

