For distinctions of the stroke subtypes regarding recurrence rates of cerebrovascular events, Kaplan-Meier curves and Cox regression analysis will be used. For categorical variables, Fisher’s exact test and for continuous variables, an unpaired t-test will be applied. All p-values <0.05 will be considered as statistically significant.

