## Discussion

This study differs from previous carotid plaque imaging studies in several ways. First, we focus on patients with cryptogenic stroke, classified by two raters and exclude patients with high grade stenosis (>70%), who usually undergo immediate invasive treatment and cannot be followed regarding plaque progression. Second, most previous studies have used a broader definition of the index event, including not only patients with a stroke documented by DWI-positive lesions on brain MRI, but also patients with TIA and amaurosis fugax [16,19], or even focused on asymptomatic patients [20,22]. Third, the time interval between the event and the MRI scan was up to 3 months [23], whereas CAPIAS includes patients within 7 days after symptom onset. Histopathological studies have shown that plaque features associated with vulnerability have the highest frequency in the first days after the ischemic event, thus suggesting that a short time period between event and MRI seems to be preferable [6,39]. Furthermore we excluded stroke patients younger than 50 years because the etiologic spectrum in this group differs from that in older subjects. The most frequent etiologic subgroups in the age range of 16–49 years are cardioembolism and arterial dissections while strokes due to large-artery atherosclerosis are extremely rare [40]. Finally, patients are systematically followed by clinical examination for 36 months and brain MRI for 12 months. Recent results of relatively small studies suggested that with improvement in best medical treatment the rate of recurrent events has decreased substantially in recent years. However, to date no larger trials are available which show the exact rate of recurrent events in ischemic stroke patients with <70% carotid artery stenosis and >2 mm atherosclerotic plaques and therefore it is impossible to provide precise estimates of the rate of stroke recurrence. In order to improve the power of the study we will use a clinical follow up period of 36 months and we will count silent ischemic lesions in the 12 months follow up brain MRI. Furthermore we will collect the number of TIA, amaurosis fugax and cardiovascular events.

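### The time-to-event recurrence endpoint is contradictory: MRI-only lesions count as events in several sections but are absent from the Cox endpoint for plaque morphology

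*Protocol article*

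**What the plan says.** Several parts of the protocol article bear on this endpoint.

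- **Secondary outcomes**, definition: "Cerebrovascular events are defined either clinically (TIA, amaurosis fugax or stroke), by brain MRI alone (new ischemic lesion on brain MRI", or by both together. The same paragraph sends unilateral anterior-circulation events, so defined, into the analysis of recurrence risk in patients with AHA-LT VI plaques.
- **Sample size**: recurrence associated with these plaques "will be determined as the time period until the next ischemic event".
- **Imaging and statistical analysis**, plaque morphology: "The effect of plaque morphology on cerebrovascular (TIA, amaurosis fugax and stroke) and cardiovascular events (myocardial infarction, vascular death) will be assessed using Cox" regression. MRI-only lesions are not listed.
- **Imaging and statistical analysis**, stroke subtypes: "For distinctions of the stroke subtypes regarding recurrence rates of cerebrovascular events, Kaplan-Meier curves and Cox regression analysis will be used".
- **Discussion**, in the sentence about improving power: "we will count silent ischemic lesions in the 12 months follow up brain MRI".
- **Abstract, Background and the first paragraph of Secondary outcomes**: the rate of new MRI lesions at 12 months is named as an outcome alongside recurrence of ischemic events.
- **Assessment and Table 2**: brain MRI is done at baseline and month 12 only. Months 3, 24 and 36 are telephone interviews.

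**The concern.** One term, cerebrovascular event, has two contents. Two analysts could each follow the text and report different hazard ratios, one with silent lesions and one without. The choice could also be made after the results are known.

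The broader content also does not suit Kaplan-Meier or ordinary Cox regression. A lesion found only on the 12-month scan has no onset date, can be found only in patients who are rescanned, and cannot be found after month 12, although clinical follow-up runs to month 36. Recurrence is one of the stated grounds for enrolling 300 patients, so the content of this endpoint should be fixed in advance.

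**Working it through.** **1. The passages side by side.** Secondary outcomes (event definition), Sample size (time to next ischemic event), the subtype sentence (Kaplan-Meier and Cox on cerebrovascular events) and the Discussion (silent lesions counted for power) together point to MRI-only lesions inside a time-to-event analysis. The plaque-morphology sentence points to clinical events only. The Abstract, the Background and the opening of Secondary outcomes allow a third reading, in which new lesions are only a 12-month rate. No sentence chooses between these.

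**2. The plan's own figure.** Inputs from Sample size: 300 patients, 8% events within 12 months, hazard ratio 5 (the plan says at least 5). Expected events by month 12: 300 × 0.08 = 24. The carrier share p in the whole cohort and the power are not stated for this calculation, so the 300 cannot be reproduced exactly. By Schoenfeld, with two-sided 5% and 80% power assumed, the events needed are (1.96 + 0.84)² / [p(1 − p)(ln 5)²]:

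| p | Events needed | Power with 24 events |
|---|---|---|
| 10% | 34 | 66% |
| 15% | 24 | 80% |
| 25% | 17 | 93% |
| 50% | 13 | 98% |

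So 300 suffices on its own inputs, with clinical events alone, if p is about 15% or more.

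**3. How much silent lesions could change the endpoint (assumed rates).** Let s be the 12-month silent-lesion risk, independent of clinical events, with everyone rescanned. First events by month 12 = 300 × [1 − 0.92(1 − s)].

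| s | First events by month 12 | Known only at the scan |
|---|---|---|
| 5% | 37.8 | 13.8 (37%) |
| 10% | 51.6 | 27.6 (53%) |
| 15% | 65.4 | 41.4 (63%) |
| 20% | 79.2 | 55.2 (70%) |

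Over 36 months the share is lower. If the 8% yearly risk stays constant with full follow-up, first events total 300 × [1 − 0.92³(1 − s)]. That is 78.1 at s = 5% and 113.1 at s = 20%, and the scan-only share is 13.8/78.1 = 18% to 55.2/113.1 = 49%.

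**4. Effect on power (assumed p = 25%, s = 10%).** Power = Φ(√[d·p(1 − p)] × ln HR − 1.96), where d is the number of events. Clinical events only: √(24 × 0.1875) × 1.609 − 1.96 = 1.45, giving 93%. For the composite, the hazard ratio is the hazard-weighted mix of 5 for clinical events and an assumed value for silent lesions:

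- Silent HR 5: composite HR 5.0, 50 events, power above 99%.
- Silent HR 2: composite HR 3.0, 51 events, power 93%.
- Silent HR 1: composite HR 2.16, 51.6 events; √(51.6 × 0.1875) × 0.770 − 1.96 = 0.43, power 67%.

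Counting silent lesions can therefore raise or lower power. The formula treats event times as exact, so these values are indicative only.

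**5. Direction of possible bias (assumed).** Take a true silent risk of 20% and a clinical risk of 8% in both groups, and suppose unscanned patients are kept as free of silent lesions. With 60% of carriers and 80% of the others rescanned, the observed silent risks are 0.20 × 0.60 = 12% and 0.20 × 0.80 = 16%. The ratio of cumulative hazards is ln(0.92 × 0.88)/ln(0.92 × 0.84) = 0.82, although the true ratio is 1. Reversing the attendance split gives 1/0.82 = 1.22, and equal attendance gives 1.00. The proportion among rescanned patients is 20% in both groups in every case.

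**The case against.** The strongest reply is that no sentence says outright that silent lesions enter the survival curves. The only Cox sentence about plaque effects lists clinical events. The Kaplan-Meier sentence concerns stroke subtypes, not plaque carriers. New MRI lesions are already named as an outcome with their own 12-month horizon, and the remark on power is Discussion text. Read generously, the plan is close to two separate endpoints. Event dating and censoring rules may also stand in an analysis plan that is not shown.

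Most of this stands as a limit on the point. A reader might infer that silent lesions definitely are in the curves; the documents support only that the text is contradictory. The contradiction remains, because the event definition and the sentence sending those events into the recurrence-risk analysis are not narrowed anywhere, and Sample size frames that analysis as time to event.

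Three further inferences go too far:

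- **Unscanned patients kept as event-free.** The article does not say this.
- **Attendance linked to outcome.** The limitations text says severely affected patients may refuse an additional MRI. It says nothing about attendance at month 12, plaque status or recurrence.
- **The T2 rule admitting the old index infarct.** The rule reads: "New ischemic lesions on brain MRI during follow up are defined as hyperintense lesions clearly visible on T2 weighted sequences". The word new implies comparison with baseline, where DWI, ADC, T2 and FLAIR are acquired, so this objection is largely met.

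**Conclusion.** The point holds as a contradiction about what the Kaplan-Meier and Cox analyses count, with a method problem that follows if silent lesions are included: undated events, detectable only in rescanned patients and only at month 12.

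The size of any bias cannot be computed, because the documents give neither a silent-lesion rate nor scan attendance. The event shares, power values and ratios under the working rest on assumed rates and show only that the endpoint choice matters and that bias could go either way or be absent. A reader might take the 0.82 as an estimate of bias; it depends entirely on an unsourced attendance split.

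Severity is moderate. This is a secondary outcome, and the primary comparison of baseline plaque prevalence is unaffected.

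**What to change.** Align Secondary outcomes, Sample size, Imaging and statistical analysis (both Cox sentences) and the Discussion as follows.

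1. Use time to first clinical cerebrovascular event (TIA, amaurosis fugax or stroke) to 36 months for Kaplan-Meier and Cox, with cardiovascular events as the plaque-morphology sentence already lists them.
2. Analyse a new lesion on the 12-month MRI as a separate yes/no outcome among rescanned patients, for example by logistic or modified Poisson regression, and report attendance by plaque group.
3. If a composite is kept, use an interval-censored method that places silent onset between the two scans and does not treat unscanned patients as known to be lesion-free.
4. Limit the Discussion's statement that silent lesions improve power to the MRI outcome.

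The cost is wording only; the schedule and sequences stay as they are. The downside is fewer events in the time-to-event model: 24 by month 12 on the plan's inputs, and about 300 × (1 − 0.92³) = 66 by month 36 if the yearly risk stays at 8%. The separate MRI analysis still assumes that, within plaque groups, attendance is unrelated to having a new lesion.
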